### Sample size

For the COMDAT trial, power is estimated for three outcomes related to primary treatment: Proportion of participants who complete treatment, proportion of participants who do not use illegal drugs within last week before recorded session (measured by WOM), and number of sessions attended. All calculations are based on an alpha of 0.05 and a power of 0.8. Power is calculated for a non-inferiority trial, as MOVE-I has already proved to be an effective form of treatment [29, 30].

The sample size needed for assessing completion of primary treatment is calculated based on a 49% completion rate from the MOVE-I trial and a 34% completion rate based on the national register of drug and alcohol treatment (SIB and NAB respectively) for 2017 [29], selected to match the inclusion criteria of the COMDAT trial. The NIS margin was set at 20% (app. 0.1). Based on these parameters, a sample size of 61 in each group is needed to evaluate this outcome.

For drug use at last recorded WOM session, a proportion of 41% vs. 31% was chosen based on ‘worst case’ from the previous MOVE trial. The NIS margin was set at 20% or 0.08. Based on these parameters, a sample size of 87 in each group is needed to evaluate this outcome.

For number of sessions attended power was based on a poisson regression of number of sessions attended in the MOVE-G and other groups from the MOVE trial with a base outcome of 0.7 and an IRR of 1.5. Based on these parameters, a sample size of 80 is needed in each group to evaluate this outcome. All power calculations were carried out using the packages TrialSize and WebPower for R (v. 3.6.1.)

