**Methods:**

A two-arm non-inferiority trial comparing MOVE-I (Pedersen et al., Drug Alcohol Depend 218:108363, 2020) with MOVE-G a combined group treatment for both alcohol use disorder and drug use disorder. The primary objective is to examine whether MOVE-G is non-inferior to MOVE-I in relation to abstinence from drug and/or alcohol, number of sessions received, and completion of treatment as planned. All participants will receive treatment based on cognitive behavioral therapy and motivational interviewing, vouchers for attendance and text reminders, as well as medication as needed (MOVE). Participants (*n* = 300) will be recruited over a one-year period at four public treatment centers in four Danish municipalities. A short screening will determine eligibility and randomization status. Hereafter, participants will be randomized to the two treatment arms. A thorough baseline assessment will be conducted approximately 1 week after randomization. Follow-up assessments will be conducted at 9 months post-randomization. In addition, patients’ use of drugs and alcohol, and patients’ wellbeing will be measured in all sessions. The main outcome measures are drug and alcohol intake at 9 months follow-up, number of sessions attended, and dropout from treatment.

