## Objectives

The primary aim of the COMDAT trial is to test the efficacy, feasibility and acceptability of MOVE-G; a treatment that combines MI, CBT, and CM in a group format offered to patients with either an alcohol use disorder, a drug use disorder, or both. The COMDAT trial will test whether MOVE-G is non-inferior to MOVE-I in relation to abstinence from drug and/or alcohol use, number of sessions received, and completion of treatment as planned.

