## Interventions

The Counselors who will provide MOVE I and G at the four sites are selected by the facility managers, based on their ability and resources (time, normal work routine) to participate in the project. This approach is pragmatic and mirrors clinical practice in substance treatment services across Denmark, and would thus be possible to replicate in a potential future national implementation. During the trial, the counsellors will frequently discuss the implementation of the two conditions, and will be supervised by a clinical psychologist with expertise in CBT and MI.

The two treatment conditions will include the following components: Baseline assessment and treatment planning in accordance with the Danish legislation (session 1 and 2, see Fig. 2), routine outcome monitoring, text reminders to attend all sessions, and vouchers worth 27 Euros handed out at every second session. Further, the two conditions both include three initial individual sessions of integrated MI and CBT (sessions three to five), where the primary focus will be how to handle high-risk situations and potential slips and relapses.

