### Outcomes

The primary outcomes are:
➢ Substance intake measured in all attended sessions using the Wellbeing and Outcome Monitoring (WOM) screening tool [24, 25]. In addition, participants will be asked about substance use within the last month (YouthMap/AdultMap) at enrolment and 9 months after enrolment [26–28].➢ Number of sessions attended measured consecutively by the counsellor responsible for the treatment offered to the participant.➢ Dropout from treatment as defined by being discharged for any reason other than having completed the primary treatment course.

The secondary outcome measures are:
➢ Psychological wellbeing (general, social contexts, close relationships) measured at each session using three items from the WOM screening.➢ Everyday functioning (concentration, planning, keeping appointments, sleep, eating habits, cleaning etc.) within the last month measured at enrolment and 9 months after enrolment (YouthMap/AdultMap).➢ Illegal activities last month at enrolment and 9 months after enrolment (YouthMap/AdultMap).➢ Employment / education activities within the last month and 9 months after enrolment (YouthMap/AdultMap).➢ Treatment fidelity (counsellors) measured by audio recording all sessions.

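### The only substance outcome with a margin and sample size (no illegal-drug use at the last recorded session) is not the declared main outcome, drug and alcohol use at 9 months

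*Protocol article*

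**What the plan says.** Five places in the protocol article describe the substance outcome.

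- **Abstract, Methods:** "The main outcome measures are drug and alcohol intake at 9 months follow-up, number of sessions attended, and dropout from treatment".
- **Objectives:** non-inferiority is to be tested on abstinence from drugs and/or alcohol. The treatment is "offered to patients with either an alcohol use disorder, a drug use disorder, or both".
- **Outcomes:** the first primary outcome is "Substance intake measured in all attended sessions using the Wellbeing and Outcome Monitoring (WOM) screening tool". Last-month use from the YouthMap/AdultMap, at enrolment and 9 months, is added in the same item.
- **Sample size:** "power is estimated for three outcomes related to primary treatment". The substance one is the "proportion of participants who do not use illegal drugs within last week before recorded session (measured by WOM"). The planning text then reads: "For drug use at last recorded WOM session, a proportion of 41% vs. 31% was chosen". The margin is 0.08 and the requirement 87 per arm, at alpha 0.05 and power 0.8.
- **Statistical analyses:** the main objective is substance use 9 months after randomisation, summarised as a total score and modelled as an ordinal outcome.

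**The concern.** A non-inferiority claim is only as good as the margin behind it, and a margin belongs to one outcome, at one time, on one scale. Here the only margin for substance use belongs to illegal drugs in the last week, at whatever session happened to be a patient's last. The trial is presented as answering a different question: drug and alcohol use at 9 months.

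Two things are at stake. First, nobody can say what power the trial has for its main objective, or what difference there would count as acceptable. Second, the powered definition leaves alcohol out although patients with alcohol use disorder alone are enrolled. If they are counted, most of their contribution is fixed regardless of how their drinking responds. That moves the arms together, which in a non-inferiority trial favours the conclusion sought.

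**Working it through.** **1. The plan's own figure.** Inputs from the Sample size section: proportions 0.41 and 0.31, margin 0.08, alpha 0.05 (taken as one-sided, since the text does not say), power 0.8.

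n per arm = [p1(1−p1) + p2(1−p2)] × (z_alpha + z_power)² / (difference + margin)²

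- Variance term: 0.41×0.59 + 0.31×0.69 = 0.2419 + 0.2139 = 0.4558
- (1.6449 + 0.8416)² = 2.4865² = 6.1827
- (0.10 + 0.08)² = 0.0324
- n = 0.4558 × 6.1827 / 0.0324 = 86.98, rounded up to 87

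The stated 87 is reproduced. The fault is not in the arithmetic but in which outcome it serves.

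**2. The definitions side by side.**

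| Section | Substance | Time | Form | Margin and n |
|---|---|---|---|---|
| Abstract, Methods | drugs and alcohol | 9 months | not stated | none |
| Objectives | drugs and/or alcohol | not stated | abstinence | none |
| Outcomes | substance intake (WOM), plus last-month use | every attended session, plus enrolment and 9 months | not stated | none |
| Sample size | illegal drugs only, last week | last session with a WOM record | binary | 0.08; 87 per arm |
| Statistical analyses | substance use | 9 months | ordinal total score | none |

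The one row with a margin matches neither the Abstract nor the Statistical analyses row on substance, time or form. Power for the 9-month outcome cannot be computed from the article: it gives no 9-month rate, ordinal distribution, margin or expected loss to follow-up.

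**3. Effect of leaving alcohol out.** Let s be the share of participants with alcohol use disorder only. Assume that they are in the denominator and use no illegal drugs in either arm. A true loss D in drug-free status among the remaining patients then appears in the whole sample as (1−s)×D. The loss that shows as exactly the margin is D = 0.08/(1−s):

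- s = 0.3: 0.08/0.7 = 0.114
- s = 0.4: 0.08/0.6 = 0.133
- s = 0.5: 0.08/0.5 = 0.160

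The article does not give s; 0.3 to 0.5 is an assumed range.

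**4. What this does to the test (illustration).** Assume 150 per arm, one-sided 0.05, margin 0.08, 41% drug-free among drug patients on MOVE-I, and a true 15-point loss among drug patients on MOVE-G.

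| s | Visible loss (points) | Chance of declaring non-inferiority |
|---|---|---|
| 0 | 15.0 | 0.2% |
| 0.25 | 11.25 | 1.4% |
| 0.5 | 7.5 | 6.0% |

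At s = 0.5 a loss nearly twice the margin among drug users has become a loss inside it.

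**The case against.** **The denominator.** The strongest reply is that the article never says alcohol-only patients are counted, and its planning rates hint that they are not. The source reads "a proportion of 41% vs. 31% was chosen based on ‘worst case’ from the previous MOVE trial", without saying whether these are rates of use or non-use. If they are non-use rates, a 40% share of automatic successes could not give an overall 31%, and a 50% share could not give 41% either; the figures would look like those of drug users. If they are use rates, the check does not apply. This stands as a limit: the dilution is conditional. But the definition speaks of participants without restriction, so the ambiguity itself needs settling.

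**The powered measure is not foreign to the plan.** Session-level WOM intake is listed first among the primary outcomes. A reader might infer that the powered endpoint is never analysed. That is too strong: the total score in the Statistical analyses section does not rule out WOM data, and an article may leave the model to a fuller document. What remains is a conflict between stated details, not an omission.

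**The sample is larger than needed.** 300 exceeds 2×87 = 174. But the surplus is nowhere tied to the 9-month outcome. The 87 also rests on a 10-point advantage for one arm. With no true difference, the same formula gives 2×0.31×0.69×6.1827/0.0064 = 414 or 2×0.41×0.59×6.1827/0.0064 = 468 per arm. That is a separate matter, noted only because the surplus cannot be assumed to cover the gap.

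**Stronger readings that the article does not support.**
- A reader might infer that dropouts' last values come from sessions identical in both arms. Sessions 1 and 2 are assessment and planning in both arms, and "the two conditions both include three initial individual sessions of integrated MI and CBT (sessions three to five"), so this is true only of those who leave by session 5. The timing of dropout is not given. Those patients would also differ little by arm at 9 months under intention-to-treat, so this is no argument against the last-session measure.
- A reader might infer that observing use only during attendance favours non-inferiority. The direction is unproven: earlier leaving on MOVE-G could make it look worse.
- A reader might infer inflated error or poor joint power from three primary outcomes. No passage lets any single success suffice; the Objectives join the three with 'and'. On the plan's own assumptions, power at 150 per arm is Φ(2.4865×√(150/n) − 1.6449). For n = 61, 87 and 80 this is about 99%, 95% and 96%, or about 90% jointly if independent.

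**Conclusion.** The concern holds in this form: the margin of 0.08 and the 87 per arm apply to illegal-drug use at the last recorded session, and the declared main outcome, drug and alcohol use at 9 months, has neither a margin nor a power statement. This follows from the article's own wording and needs no assumption.

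The second part is conditional. If alcohol-only patients are in the denominator and use no illegal drugs, a true loss of 11 to 16 points among drug users shows as 8 points for a 30-50% share. Both the share and their inclusion are assumptions. The article does not show that the powered measure is biased towards non-inferiority in any other way.

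**What to change.** Reconcile the Abstract, Outcomes, Sample size and Statistical analyses sections:

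1. Name one primary substance outcome for all randomised patients that includes alcohol, at the 9-month YouthMap/AdultMap interview. An example is last-month abstinence from the participant's problem substance or substances.
2. Attach the non-inferiority margin to that outcome, on the scale on which it will be analysed, and restate the power at the planned 300 with an allowance for loss to follow-up.
3. Label the last-session WOM measure supportive, say that the 87 per arm applies to it only, and state its denominator and whether 41% and 31% are rates of use or non-use.

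Completion and number of sessions attended can stay as they are.

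The cost is protocol and registry wording, since both instruments are already collected. The downside is fewer analysed patients: with assumed losses of 10%, 20% or 30%, 300 becomes 270, 240 or 210. The restated power may be less favourable than the figure now printed.

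### The 61 and 87 per group are reproduced only by crediting the new arm with an unstated 15- and 10-point advantage; with equally good formats, 150 per arm falls well short of 80% non-inferiority power

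*Protocol article*

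**What the plan says.** The Sample size section of the protocol article says "Power is calculated for a non-inferiority trial, as MOVE-I has already proved to be an effective form of treatment" and adds that "All calculations are based on an alpha of 0.05 and a power of 0.8". It does not say whether alpha is one- or two-sided.

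- **Completion:** the size is "calculated based on a 49% completion rate from the MOVE-I trial and a 34% completion rate based on the national register". Then "The NIS margin was set at 20% (app. 0.1"), and "a sample size of 61 in each group is needed to evaluate this outcome".
- **Drug use:** "a proportion of 41% vs. 31% was chosen based on ‘worst case’ from the previous MOVE trial". Then "The NIS margin was set at 20% or 0.08", with 87 per group as the result.

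The Methods part of the Abstract plans 300 participants in two arms. Objectives names abstinence, sessions received and completion as the outcomes on which MOVE-G is to be shown non-inferior to MOVE-I. The Sample size section assigns no rate to MOVE-G. It also does not say how 300 follows from 61, 87 and the 80 per group given for sessions attended, a third calculation that was not checked here.

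**The concern.** A non-inferiority size depends on the assumed true difference as well as the margin. If the new arm is assumed better, the required number drops sharply, so that assumption has to be visible. Here two different rates enter each calculation. The only one tied to a treatment in this trial is 49%, and it belongs to the comparator. The 34% comes from a national register, which is not an arm.

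Sizes as small as 61 and 87 with margins of 0.1 and 0.08 suggest that the gap between the rates was counted in favour of the new arm. If so, the 80% power rests on a substantial superiority of MOVE-G that the article does not claim. A reader comparing 87 with 150 per arm would take the trial to have ample room, when under equality it does not.

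**Working it through.** **Inputs.** From Sample size: rates 49%/34% and 41%/31%; margins about 0.1 (20% of 0.49 = 0.098) and 0.08; power 0.80; alpha 0.05, taken both as one-sided 0.05 and as one-sided 0.025. From the Abstract: 300 in total, taken as 150 per arm. Equal allocation and no losses are assumptions.

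**Formula** (unpooled variance): n per arm = (z_α + z_β)² × [p₁(1−p₁) + p₂(1−p₂)] / (d + M)², where d is the true advantage of the new arm and M the margin. (z_α + z_β)² is 6.183 at one-sided 0.05 and 7.849 at one-sided 0.025.

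**1. Reproducing the stated sizes, gap credited to the new arm**

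- Completion: variance sum 0.2499 + 0.2244 = 0.4743. At one-sided 0.025 with M = 0.098: 7.849 × 0.4743 / 0.248² = 60.5, so 61.
- Drug use: variance sum 0.2419 + 0.2139 = 0.4558. At one-sided 0.05 with M = 0.08: 6.183 × 0.4558 / 0.18² = 86.98, so 87.

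None of these alternatives gives 61 or 87: zero difference at the printed margins; the gap counted against the new arm; 20% as an absolute margin with zero difference (completion 70 to 99, drug use 67 to 95 depending on rate and alpha, nearest 84 and 90); a superiority test (133 to 182 and 284 to 381); equivalence at zero difference (429 and 648).

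**2. One alpha?**

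- One-sided 0.05, completion with M = 0.10: 6.183 × 0.4743 / 0.25² = 46.9, so 47, not 61.
- One-sided 0.025, drug use with M = 0.08: 7.849 × 0.4558 / 0.18² = 110.4, so 111, not 87.
- One-sided 0.05, completion with M = 0.07: 6.183 × 0.4743 / 0.22² = 60.6, so 61.

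A single alpha of one-sided 0.05 therefore fits both figures only if the completion margin was near 0.07. That is close to 20% of 34% (0.068) but is not the printed value. The favourable gap is needed in either case.

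**3. The rates read as labelled.** If MOVE-I has 49% and MOVE-G 34%, the deficit of 0.15 exceeds the margin, non-inferiority is false, and power at 150 per arm is under 1%. A 10-point deficit on drug use likewise exceeds 0.08 (power about 1–2%).

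**4. Equal true rates (d = 0), 80% power**

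| Outcome | One-sided 0.05 | One-sided 0.025 |
|---|---|---|
| Completion, 49%, M = 0.098 | 6.183 × 0.4998 / 0.098² → 322 | 7.849 × 0.4998 / 0.098² → 409 |
| Drug use, 41%, M = 0.08 | 6.183 × 0.4838 / 0.08² → 468 | 7.849 × 0.4838 / 0.08² → 594 |

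**5. Power with 150 per arm:** Φ((d + M)/SE − z_α)

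- Completion, d = 0: SE = √(0.4998/150) = 0.0577; 0.098/0.0577 = 1.698; power 52% / 40%.
- Drug use, d = 0: SE = √(0.4838/150) = 0.0568; 0.08/0.0568 = 1.409; power 41% / 29%.
- Completion, d = 0.05 (54% v 49%): SE = √((0.2484 + 0.2499)/150) = 0.0576; 0.148/0.0576 = 2.57; power 82% / 73%.
- Drug use, d = 0.05 (46% v 41%, read as non-use): SE = √((0.2484 + 0.2419)/150) = 0.0572; 0.13/0.0572 = 2.27; power 74% / 62%.

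At the sizes the article calls needed, power under equality is 29% / 19% for completion (61 per arm) and 28% / 19% for drug use (87 per arm).

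**The case against.** The strongest reply is that equality is not the only planning case. The Background cites a meta-analysis with a small significant benefit of group over individual therapy on abstinence, and the Discussion allows for a superior or similar MOVE-G. If the built-in 15- and 10-point gains were real, 150 per arm would give over 99% and 90–95% power. This stands as far as it goes: a modest MOVE-G advantage is a legitimate assumption. But the Background calls the effect small and reports no significant effect on attrition. Nothing in the article supports 10 or 15 points, and Sample size claims no advantage at all.

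It can also be said that the power figures here are not those of the main planned analysis. That is right. Statistical analyses centres on an ordinal summary of substance use at 9 months in an adjusted model, whereas these figures are for unadjusted binary comparisons of the outcomes that Sample size itself uses. They test the article's sample-size claim and do not predict the trial's result.

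Some stronger readings are tempting but not supported:

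- **Two alphas were used.** A misprinted completion margin explains the figures equally well.
- **MOVE-I's advantage over usual care was knowingly reused as MOVE-G's advantage over MOVE-I.** The 49%/34% labels fit that account, but no arms are named for 41%/31%, and a sign slip in the software would give the same numbers. The favoured direction is inferred from the formula.
- **An inconclusive result will be reported as group treatment being worse.** Nothing in the article says so.

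Finally, this is not detail that an article leaves to a fuller document. The inputs and results are printed together and do not support the stated power.

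**Conclusion.** The point holds. The 61 and 87 per group depend on an unstated advantage of 15 and 10 points for the new arm, which the article does not justify and which its only arm label contradicts. At the printed margins, either the alpha or the completion margin is misstated; the document does not allow one to say which.

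If the two formats are truly equal, 150 per arm gives roughly 40–52% power for completion and 29–41% for drug use, not 80%. A true MOVE-G advantage of 5 points brings only completion at one-sided 0.05 past 80%. These figures assume 1:1 allocation, no losses, no clustering and comparator rates of 49% and 41%. Using the lower printed rates changes little: at zero difference, 34% with margin 0.098 gives 56%/43% and 31% with margin 0.08 gives 44%/32%.

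A reader might infer that the trial is bound to fail on these outcomes. That does not follow, because the shortfall is conditional on a true difference at or near zero.

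**What to change.** Keep the 300 participants and rewrite the sample-size paragraph:

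1. Withdraw 61 and 87 as the numbers needed for 80% power.
2. Say which rate belongs to which arm, and whether 41% and 31% are use or non-use.
3. State the assumed true difference: zero, or a MOVE-G gain with its justification.
4. State one alpha with its sidedness, and one margin per outcome.
5. Report the power that 150 per arm gives under those assumptions.
6. State that a confidence interval crossing the margin is inconclusive and is not evidence that MOVE-G is inferior.

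The margin should not be widened to suit the sample; it has to rest on what loss is acceptable. The cost is a rewritten paragraph and a less favourable stated power. The change corrects what is disclosed but adds no power, and it needs no extra participants.

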### Assignment of interventions

Randomization will be performed by means of the minimization method, using Minim randomization software, which is a biased-coin approach with a probability of 0.7 to 0.8 for allocation of the “best fitting” treatment [31]. The minimization method was chosen to obtain an overall balanced distribution of participants, as the number of expected participants was too small for true randomization (e.g. a coin toss or random numbers generator). Furthermore, participants will be randomized at each site, in order to obtain an equal distribution within each treatment center/municipality.

